### Stool sample testing

Stool samples from all participants will be tested for bacteria and viruses. For children who do not provide a stool specimen prior to discharge, rectal swabs will be performed. For patients enrolled at HSC and Alberta Children’s Hospital (ACH), additional stool samples will be collected on Days 5 and 28 for sIgA testing.

### Randomization

#### Sequence generation

We used http://www.randomize.net to produce the study randomization lists stratified by site. The lists were sent to the central pharmacy at ACH where an independent research pharmacist prepared consecutively numbered kits according to the randomization schedule. The kits were couriered directly to the sites using insulated shipment containers and temperature monitors.

#### Allocation concealment

The site http://www.randomize.net uses industry standard security to send data over the internet. Randomization employed random blocks of 4 and 6 with a 1:1 allocation ratio.

#### Implementation

A log of all screened patients is being maintained. If consent is obtained, study staff collects baseline demographic clinical variables and complete the data collection forms. Study staff then log into http://www.randomize.net to randomize the patient.

### Bias

The probiotic and placebo powders are identical in appearance, taste, texture and smell. Participants, families, healthcare providers, data collectors, outcome adjudicators, and data analysts are blinded. Co-interventions and other sources of confounding are being recorded. The trial has been registered at http://www.clinicaltrials.gov (NCT01853124).

### Concomitant medications

The concomitant administration of antibiotics is permitted as probiotics remain effective when given concomitantly with antibiotics [43]. Their use is at the discretion of the child’s treating physician. Similarly, antipyretics, anti-emetics, and other medications may be administered. ORS will be provided during the ED visit. Discharge instructions will be provided.

### Outcomes

#### Primary outcome (clinical)

The primary outcome is the development of moderate to severe disease in the 2 weeks after the index ED visit as measured by the MVS (Table 1) [44]. The original 20 point Vesikari Score, which has been employed as a dichotomous variable in many clinical studies [45-53], correlates with other meaningful measures such as caregiver anxiety, helplessness, stress, [54] parental worry, behavioral changes, and impact on the parents’ daily activities and distress [55]. However, percent dehydration, an element of the original score, is challenging to quantify due to difficulties in collecting follow-up weights, determining when rehydration has occurred, and the variation related to timing of voiding, stooling, eating, and drinking. Thus, this element is omitted or incorrectly assigned in many studies. The modified score includes an important and easy to obtain outcome that reflects global disease severity - need for unscheduled healthcare provider visits within 2 weeks of the index visit [44]. This is supported by evidence that the utilization of professional medical care correlates with disease severity [54].

**Table 1 T1:** Modified Vesikari Scale

**Points**	**0**	**1**	**2**	**3**
**Diarrhea duration**	0	1 to 96 hours	97 to 120 hours	≥121 hours
**Maximum number of diarrheal stools/24-hour period**	0	1 to 3	4 to 5	≥6
**Vomiting duration (d)**	0	1 to 24 hours	25 to 48 hours	≥49 hours
**Maximum number of vomiting episodes/24-hour period**	0	1	2 to 4	≥5
**Maximum recorded fever**	<37.0˚C R	37.1 to 38.4˚C R	38.5 to 38.9˚C R	≥39.0˚C R
**Future healthcare visit**	0%	-	Primary care	Emergency department
**Treatment**	None	Rehydration	Hospitalization	-

R, rectal.

Follow-up will occur daily until both the diarrhea and vomiting have resolved. On Day 14 each variable is assigned a score for the entire study period (Time 0 to Day 14); each patient gets a single total score for the study. Variables are scored based on the worst 24-hour period or on the total duration of symptoms or are based on the occurrence of an outcome.

Regardless of the score assigned at Time 0 (that is, the pre-enrollment score), everyone reverts to a score of 0 at enrollment. The pre-enrollment score will serve as a covariate in a secondary analysis of the primary outcome and will be employed for subanalysis purposes. The primary outcome will only include symptoms and outcomes that occur following the ED visit and will not be directly impacted by the pre-enrollment score.

With the original score, severe disease was defined as ≥11 [45,46,51,52,56-58] and moderate as ≥9 [59]. In the derivation study, [44] construct validity was proven by using scores of ≥9 to define moderate and ≥11 to define severe disease. These cut-points were associated with significant increases in other measures of disease severity (for example, daycare (*P* = 0.01) and work absenteeism (*P* = 0.002)) [44].

#### Secondary outcomes

Clinical secondary outcomes are:

1. duration of diarrhea, which is time from treatment initiation until the appearance of the last watery stool [60-62].

2. duration of vomiting. Recovery will be evaluated in children who vomit ≥3 times over the 24 hours prior to the ED visit, and duration is defined as ‘time from treatment initiation until last vomiting episode’.

3. return visits for unscheduled care to a healthcare provider related to vomiting, diarrhea, dehydration, fever, or fluid refusal, within two weeks. Scheduled visits will not be included.

4. work and daycare absenteeism.

#### Safety

To determine if short course probiotic administration to young children with AGE is associated with an increase in minor side effects, groups will be compared regarding the development of any side effects with particular attention paid to bloating or abdominal distention (grouped for analysis), duration of fever, and buttock rash.

#### Mechanism

To determine if probiotic administration increases fecal sIgA levels in children with AGE, the first stool sample produced following enrollment will be collected along with samples on Days 5 and 28. We will determine if fecal sIgA levels are greater among children treated with a probiotic agent compared with placebo. Levels will be correlated with clinical findings.

### Data retrieval

1. Daily Telephone/Electronic Survey Communication: At the index visit, caregivers will be asked their preferred method of communication - electronic versus telephone. Caregivers will be contacted daily by the identified method until both the diarrhea and vomiting have resolved. A standardized collection form will be employed. Detailed questioning will follow positive responses. Compliance will be assessed on Day 5. To maximize validity, caregivers will be reminded of the importance and method of administering the probiotic/placebo.

2. Chart Review: We will verify data regarding revisits, intravenous hydration, hospitalization, and microbiology testing using each center’s medical record database.

3. Database Reviews: Provincial databases and Canadian Institute for Health Information databases will be employed to verify future health care provider use.

### Health service research issues

An economic evaluation will be conducted alongside the RCT. The incremental cost effectiveness will be determined by assessing resources and costs associated with the treatment of AGE for children who receive the current standard of care compared to those who receive a probiotic.

### Sample size estimates

#### Clinical

The sample size estimate was based on the assessment of the between-group difference in proportions of children with a post-randomization score ≥9 on the MVS. The adoption of probiotic use can be recommended if the proportion of the primary outcome is significantly lower among those who receive the probiotic medication. Calculations were based on a two-sided α of 0.05 and power of 0.90. The null hypothesis is *H*_
*0*
_: *P*_
*c*
_ - *P*_
*I*
_ = 0, where *P*_
*I*
_ and *P*_
*C*
_ are the outcome probabilities in the intervention and control groups, respectively. The alternative hypothesis is *H*_
*A*
_*:│P*_
*I*
_ - *P*_
*C*
_*│* >0.10. Ten content experts from the United States and Canada were surveyed regarding the minimal clinically important difference; absolute risk differences ranging from 7.5 to 15% were suggested. A conservative estimate of 10% was selected for the primary outcome.

Our estimate for the development of moderate to severe AGE in the controls is based on data collected as part of two evaluations of the MVS in nearly 750 children in U.S. [63] and Canadian EDs. [44] Approximately 25% of eligible children had scores consistent with moderate to severe disease. Employing a baseline probability of 25% in the controls, the required sample size to compare proportions between two groups is 670 [64]. Based on previous work by our group [65-67], we assume a 10% loss to follow-up, 5% drop out, and 2.5% drop in probabilities. Adjustment for O’Brien-Fleming monitoring boundaries requires a further 2% increase. Thus, the final sample size required is 886.

#### Safety

RCTs employing probiotics have not attributed any adverse events to probiotic administration [11]. Given our sample size, a significant difference between groups will be easily detected.

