## Methods/Design

### Hypotheses

In children aged 3 to 48 months of age who present with less than 72 hours of AGE-like symptoms to an ED, the administration of a probiotic agent when compared with a placebo:

1. will result in a significantly lower proportion of children developing moderate to severe disease over the subsequent 2 weeks.

2. will not be associated with a significantly greater occurrence of minor side effects.

3. will be associated with a greater increase in secretory IgA (sIgA).

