### Statistical analysis

All analyses will be undertaken by the intention-to-treat principle. Adverse events will use the ‘as treated’ principle. Patients who drop out or crossover will be followed and included. All statistical tests will be two-sided. Baseline characteristics will be compared between groups using frequency counts and percentages for discrete variables, and means, medians, standard deviations, and interquartile ranges for continuous variables. Sensitivity analyses will be performed to assess the possibility and consequences of losses to follow-up not occurring at random.

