#### Safety

The proportions of children experiencing any side effect, as reported by the caregivers, will be compared between groups using the Mantel-Haenszel test, stratified by site. The analysis will evaluate the presence/absence of side effects, as an aggregate outcome variable.

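### The claim that a side-effect difference will be easily detected is unsupported and holds only for large differences, yet the safety hypothesis rests on non-significance with no margin

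*Protocol article*

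**What the plan says.** Safety is one of the three key outcomes in the Abstract. Under Hypotheses, the second states that the probiotic "will not be associated with a significantly greater occurrence of minor side effects". No non-inferiority margin accompanies it.

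Under Sample size estimates, Safety, the whole justification is two sentences: "RCTs employing probiotics have not attributed any adverse events to probiotic administration", and then "Given our sample size, a significant difference between groups will be easily detected". By contrast, the Clinical and Mechanism parts of the same section each give a difference, a power and a resulting number of children.

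Under Outcomes, Safety, the groups are to be compared on any side effect, with "particular attention paid to bloating or abdominal distention (grouped for analysis), duration of fever, and buttock rash". Under Statistical analysis, Safety, the only test described is a site-stratified Mantel-Haenszel test of any caregiver-reported side effect: "The analysis will evaluate the presence/absence of side effects, as an aggregate outcome variable".

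The later Safety section, on monitoring, lists abdominal distension and fever among the events expected from the illness itself. Both also appear as side effects under Study questions, Side effect profile.

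**The concern.** The sentence is a claim about power, and a trial has power only against a stated difference from a stated rate. Neither is given. The sample size was chosen for a 10-point difference in a different outcome, so nothing in the document shows that it suits side effects. The preceding sentence, that earlier trials attributed no events to probiotics, points if anything toward rare effects, for which power is low.

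The form of Hypothesis 2 raises the stakes. When the hoped-for conclusion is the absence of a significant increase, low power works in its favor. A reader told that differences are easily detected is likely to take a non-significant result as reassurance.

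The analysis variable adds a second difficulty. A single yes/no variable that includes symptoms of the disease may hide an increase in one effect. It also does not match the outcomes section, which names three specific effects, one of them a duration.

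**Working it through.** **Inputs.** From the protocol: 886 children allocated 1:1, so 443 per arm; 10% loss to follow-up, so 886 × 0.90 / 2 = 398.7, taken as 399 per arm. On sidedness: "All statistical tests will be two-sided". The side-effect rate in controls is not given; 1% to 50% is assumed throughout.

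**The plan's own figure.** For the primary outcome, "Calculations were based on a two-sided α of 0.05 and power of 0.90", and "A conservative estimate of 10% was selected for the primary outcome". With control rate 0.25, intervention rate 0.15 and mean rate p̄ = 0.20:

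n per arm = [1.96√(2p̄(1−p̄)) + 1.2816√(p₁(1−p₁) + p₂(1−p₂))]² / (p₁−p₂)² = [1.96 × 0.5657 + 1.2816 × 0.5612]² / 0.01 = 334.2, so 335 per arm and 670 in total, as stated. Inflating, 670 × 1.02 / 0.90 / 0.925² = 887.5, close to the stated 886. The sample size is therefore sound for the primary outcome, and it contains no side-effect input.

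**Power for a side effect.** Power = Φ{[Δ√n − 1.96√(2p̄(1−p̄))] / √(p₁(1−p₁) + p₂(1−p₂))}. For 10% versus 15% at n = 399: 0.05 × √399 = 0.9987; 1.96 × 0.4677 = 0.9167; (0.9987 − 0.9167) / 0.4664 = 0.176; Φ(0.176) = 57%.

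Results at 399 per arm, with 443 per arm in brackets:

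| Assumed control rate | Rise needed for 80% power, points | Power for +5 points | Power for +10 points |
|---|---|---|---|
| 1% | 3.1 (2.9) | 97% (98%) | over 99% |
| 5% | 5.3 (4.9) | 77% (81%) | over 99% |
| 10% | 6.7 (6.4) | 57% (61%) | 98% (99%) |
| 20% | 8.5 (8.0) | 39% (43%) | 90% (93%) |
| 30% | 9.4 (8.9) | 33% (36%) | 84% (88%) |
| 50% | 9.9 (9.4) | 29% (32%) | 81% (85%) |

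For rare events, power at 399 per arm is 21% for 1% versus 2% and 38% for 2% versus 4%. The normal approximation is rough at these rates.

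**What a null result would exclude.** The 95% half-width for the difference is 1.96√(2p(1−p)/n). At p = 0.30 and n = 399 this is 1.96 × √(0.42/399) = 0.064. An observed difference of zero would leave a rise of about 6 points inside the interval. The half-width is about 4.2 points at 10% and 6.9 at 50%.

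**Effect of pooling.** Assume the other side effects are independent of the one that changes. The aggregate rate is then 1 − (1 − background)(1 − component). At 399 per arm, one effect doubling from 5% to 10% has 77% power alone. In the aggregate:

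- background 10%: 14.5% versus 19.0%, power 40%
- background 20%: 24.0% versus 28.0%, power 25%
- background 30%: 33.5% versus 37.0%, power 18%
- background 50%: 52.5% versus 55.0%, power about 10%

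The opposite case is several effects each rising from 5% to 8%. Power is about 40% for one effect, and 67%, 82% and 91% for two, three and four pooled.

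**The case against.** The strongest reply is that the document gives no figure to refute. Every rate above is assumed, so a reader who infers that the statement is simply false goes too far. The one difference of interest in the protocol is 10 points, set for the primary outcome. A rise of that size in side effects has about 81% power or more at every assumed rate, and a doubling from 10% or more has about 98% or more. This stands: the claim is unsupported, and it is right for large differences.

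A reader might also infer that pooling necessarily weakens the safety analysis. The documents do not support that. Pooling costs power when one effect rises against common background symptoms and gains it when several rise together. No background rate is given.

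Nor does the protocol say that a null result will be reported as proof of safety, or that a real side effect will be missed. Both are risks arising from how Hypothesis 2 is worded. Hypothesis 2 concerns minor side effects; serious events have separate reporting and committee review.

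Finally, the outcomes section already promises attention to the named effects, and a condensed article may leave component tables to an analysis plan that is not shown. This stands in part: missing tables are no fault. But the easy-detection sentence is a positive assertion, and the hypothesis wording is fixed in the article itself.

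**Conclusion.** The concern holds in limited form. The statement on detectability has no basis in the document and does not hold for moderate or rare effects: 5-point rises from control rates of 10% to 50% have about 57% down to 29% power at 399 per arm, and 61% down to 32% even with no losses. Combined with a hypothesis that is met by non-significance, this invites more reassurance than the data could give.

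The mismatch between the two safety sections is real but smaller. A yes/no aggregate cannot express duration of fever, and it may dilute an isolated increase.

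These sizes rest on assumed control rates, a 10% loss, the normal approximation without site stratification and, for pooling, independence. The point should be fixed, but it is not critical: the sentence drives no design choice, and the sample size stands on the primary outcome.

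**What to change.** 1. In Sample size estimates, Safety, replace the easy-detection sentence with the differences detectable at 80% power over a range of assumed control rates, labeled as assumptions.
2. Align Statistical analysis, Safety with Outcomes, Safety. Beside the aggregate, report bloating or distention and buttock rash as center-stratified risk differences, and fever duration as a center-stratified difference in duration, each with a 95% confidence interval.
3. Reword Hypothesis 2 so that its conclusion rests on the upper confidence limit for the difference rather than on non-significance. If a formal claim of no important increase is wanted, the investigators must state in advance the largest increase they would accept.

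The cost is a less favorable stated property, several safety estimates instead of one, and a few more tables. No extra children or visits are needed, since the article says the expected symptoms are recorded in routine study data collection and the named effects are already outcomes.

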#### Mechanism

A study evaluating the impact of formula supplementation with oligosaccharides found fecal sIgA values of 729 and 377 μg/g in the intervention and control groups, respectively [68]. Assuming a clinically significant difference of 300 μg/g, a standard deviation of 500 μg/g, 80% power and a type I error of 0.05, the required sample size is 45 subjects/group. We will recruit 100 patients to provide multiple stool samples for this phase of the study.

### Statistical analysis

All analyses will be undertaken by the intention-to-treat principle. Adverse events will use the ‘as treated’ principle. Patients who drop out or crossover will be followed and included. All statistical tests will be two-sided. Baseline characteristics will be compared between groups using frequency counts and percentages for discrete variables, and means, medians, standard deviations, and interquartile ranges for continuous variables. Sensitivity analyses will be performed to assess the possibility and consequences of losses to follow-up not occurring at random.

#### Clinical

The proportion of children with moderate to severe disease will be analyzed by utilizing a Mantel-Haenszel test, stratified by clinical center. Significance for the primary outcome measure will be determined using a two-sided 0.05 level. Secondary analyses of the primary outcome will employ logistic regression methods to adjust for covariates that may be imbalanced between groups. We will analyze the MVS as a continuous variable through a stratified Wilcoxon rank-sum test. The overall significance level for statistical tests on the secondary outcomes will be set at 0.05. Holm’s method will be used to adjust for multiple comparisons. The continuous variables of duration of diarrhea and vomiting will be measured in hours and analyzed with a Van Elteren test, stratified by clinical center. Unscheduled healthcare visits will be analyzed using a Mantel-Haenszel test, stratified by clinical center. The tertiary outcomes of the number of days the child is absent from daycare and the days the caregiver is absent from work will be analyzed using an appropriate model with robust estimates for standard errors. Dichotomous outcomes to be evaluated but unlikely to achieve significance include ED revisits, intravenous rehydration, and hospitalization. Additional analyses involving these outcomes will include linear and logistic regression models that adjust for possible effects of baseline characteristics.

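### The primary test is valid but leaves the pre-enrollment severity score unused, and the adjusted analysis is tied to chance imbalance instead of a fixed prognostic set

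*Protocol article*

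**What the plan says.** Protocol article, Statistical analysis, Clinical: the proportion with moderate to severe disease "will be analyzed by utilizing a Mantel-Haenszel test, stratified by clinical center", at a two-sided 0.05 level. The next step is described as follows: "Secondary analyses of the primary outcome will employ logistic regression methods to adjust for covariates that may be imbalanced between groups". No covariate is named there, and no criterion for imbalance is given.

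Protocol article, Primary outcome (clinical): every child has a score at Time 0, but scoring restarts from zero at enrollment, so the outcome counts only what happens after the ED visit. The Time 0 score has one stated analytic role besides subanalysis: "The pre-enrollment score will serve as a covariate in a secondary analysis of the primary outcome".

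Randomization (Sequence generation) is stratified by site only. The Planned subgroup analyses do not list the pre-enrollment score.

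**The concern.** Presenting severity is a natural candidate predictor of later severity. It is already recorded, and the randomization does not balance it. Leaving it out of the primary comparison forgoes whatever precision it offers.

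The second issue is the rule for the adjusted analysis. In a randomized trial any baseline difference is chance. A balanced covariate that predicts the outcome still adds precision; an imbalanced covariate that does not predict the outcome adds nothing. A rule that refers to imbalance points at the wrong property, and imbalance is known only once the arms are compared. The Outcomes section works on a different basis, naming one covariate in advance. The two sections should describe the same adjusted analysis and do not.

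At stake are a possible small gain in power and an adjusted result whose covariates nobody can later say were chosen to suit the data.

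**Working it through.** **Inputs from the article (Sample size estimates, Clinical).** "Calculations were based on a two-sided α of 0.05 and power of 0.90". "A conservative estimate of 10% was selected for the primary outcome". "Employing a baseline probability of 25% in the controls, the required sample size to compare proportions between two groups is 670". For attrition, "we assume a 10% loss to follow-up, 5% drop out, and 2.5% drop in probabilities". For interim looks, the O'Brien-Fleming "monitoring boundaries requires a further 2% increase".

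**Input not in the article.** The prognostic strength of the pre-enrollment score is assumed, as an odds ratio per SD from 1.0 to 3.0 (AUC about 0.50 to 0.76).

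**Step 1: reproduce the plan's figures.** With pooled variance and no continuity correction, 25% versus 15%, mean 20%:

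n per arm = [1.960·√(2·0.20·0.80) + 1.2816·√(0.25·0.75 + 0.15·0.85)]² / 0.10² = (1.1087 + 0.7193)² / 0.01 = 334.2, rounded up to 335, or 670 in total. Power at 335 per arm is 0.901.

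Inflation: 670 / 0.90 / 0.925² × 1.02 = 887.5, or 670 × 1.02 / (0.90 × 0.95² × 0.975²) = 885.1. Both lie within 2 children of the stated 886. The planned 90% power therefore belongs to a comparison with no baseline adjustment.

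**Step 2: what adjustment would add.** Simulation with 670 children, five centers, 1:1 within center, a standard normal baseline score, marginal risks of 25% and 15%, and 4,000 runs per setting. The center-stratified Mantel-Haenszel test is compared with a logistic model containing treatment, center and score (Wald test).

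| Assumed odds ratio per SD | AUC | Mantel-Haenszel, center | Logistic, center and score | Gain (points) |
|---|---|---|---|---|
| 1.0 | 0.50 | 89.93% | 89.85% | −0.1 |
| 1.3 | 0.57 | 90.63% | 90.85% | 0.2 |
| 1.5 | 0.61 | 89.95% | 90.73% | 0.8 |
| 2.0 | 0.68 | 90.55% | 92.38% | 1.8 |
| 2.5 | 0.73 | 90.85% | 93.98% | 3.1 |
| 3.0 | 0.76 | 90.53% | 94.30% | 3.8 |

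The simulation error of one entry is √(0.90 × 0.10 / 4,000) = 0.47 points. Both tests use the same simulated data, so the gain within a row is less noisy than differences between rows.

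**Step 3: the same question with attrition built in.** Evaluable children: 886 × 0.90 ≈ 798. Diluted risks: 0.975 × 25% + 0.025 × 15% = 24.75% for control, and 0.95 × 15% + 0.05 × 25% = 15.5% for probiotic. With 3,000 runs, unadjusted versus adjusted power was 0.899/0.906, 0.894/0.904, 0.896/0.919 and 0.910/0.933 at log odds ratios per SD of 0.3, 0.5, 0.7 and 0.9 (odds ratios 1.35 to 2.46). The gains are 0.7 to 2.3 points, in line with Step 2.

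**Step 4: adjusting only when the score is imbalanced.** The article states no such test; p<0.10 was taken as one concrete version of an imbalance rule. At an odds ratio of 3.0, power is 91.4%, against 94.3% with adjustment always applied, so most of the gain is lost.

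**Step 5: type I error, 25% in both arms.** Mantel-Haenszel by center 4.6% to 5.4%; always adjusted 4.6% to 5.2%; adjusted only if imbalanced 4.4% to 5.2%. With a simulation error of √(0.05 × 0.95 / 4,000) = 0.34 points, all are compatible with 5%.

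**The case against.** The strongest reply is that nothing here is broken. The primary test is fixed in advance, matches the site-stratified randomization and carries its planned power. The article makes it the test that decides significance and labels the logistic models secondary, so precedence is clear if the two disagree. All of this stands.

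The score may also predict only weakly. Entry requires under 72 hours of symptoms, and Table 1 gives diarrhea of 1 to 96 hours a single point, so that item hardly varies at entry. The healthcare-visit item concerns care after the index visit. A strong association cannot be presumed, and the gain may be near zero. This stands too, and is why the range starts at 0.

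A covariate list for a secondary model is normally left to the SAP, which is not shown. Its absence is no fault. But the article does more than leave the list open: it states a basis for adjustment, the basis is a poor one, and it differs from the article's own Outcomes section. An SAP list would have to override that wording.

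Some stronger readings are tempting. A reader might infer that the trial loses power; Step 1 shows it keeps what was planned. A reader might infer that the primary estimate is biased by chance differences in severity; such variation is already covered by the unadjusted test's standard error. A reader might infer that covariates will be picked by a test after unblinding; the text states no test, threshold or timing. A reader might infer that the score is disregarded altogether; the Outcomes section names it in advance for a secondary analysis.

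**Conclusion.** The point holds as a modest improvement in efficiency and prespecification. It is not an error, a bias or a shortfall against the stated power.

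The primary analysis forgoes 0 to about 4 points of power for assumed odds ratios of 1.0 to 3.0 per SD, and under 1 point for odds ratios up to 1.5. Its type I error is unaffected either way. The imbalance wording touches only the secondary adjusted analysis, where it is the wrong criterion and does not line up with the score named in advance.

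The size rests on the assumed prognostic strength. The simulations also take a single normally distributed score, no center effect on risk and no interim looks. The case for a fixed covariate set does not depend on those assumptions; the case for moving the score into the primary analysis does, and is therefore the less compelling part.

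**What to change.** Before any unblinded look, make these changes.

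- In Statistical analysis, Clinical, replace the imbalance wording with a fixed prognostic set: center and pre-enrollment MVS as a continuous term, with age optional. Align the Outcomes section so that both describe one adjusted analysis.
- Preferably make that adjusted logistic model the primary analysis. Report the standardized (marginal) risk difference with a 95% CI, which stays on the absolute scale used for the 10-point target. Keep the center-stratified Mantel-Haenszel test as a sensitivity analysis.
- If the sponsor prefers to keep the Mantel-Haenszel test as primary, the fixed set should still govern the secondary adjusted analysis.

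The cost is wording only: no new data and no change to the sample size of 886. The small downside of the preferred option is that the primary test becomes model-based. On timing, the Trial status section reports 152 children enrolled, below the 200 at which the first planned interim efficacy review takes place.

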#### Inclusion criteria

All of the following must be met for inclusion:

1. ≥ 3 watery stools in a 24-hour period [37]

2. duration of vomiting or diarrhea <72 hours

3. age 3 to <48 months

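### The deciding tests of diarrhea and vomiting duration stratify by center only and leave time since symptom onset unused: they are valid, but may give up precision

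*Protocol article*

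**What the plan says.** Under Secondary outcomes, diarrhea duration is the "time from treatment initiation until the appearance of the last watery stool" and vomiting duration is the "time from treatment initiation until last vomiting episode". The second is evaluated only in children who vomited at least three times in the 24 hours before the visit. Inclusion criteria admit children with "duration of vomiting or diarrhea <72 hours".

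Under Statistical analysis, Clinical, both durations are to be "analyzed with a Van Elteren test, stratified by clinical center". The secondary outcomes share an overall 0.05 level with Holm's adjustment. That section closes with additional analyses that "will include linear and logistic regression models that adjust for possible effects of baseline characteristics", without naming the characteristics. Sequence generation stratifies randomization by site only.

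On baseline information, Implementation says that before randomization "study staff collects baseline demographic clinical variables and complete the data collection forms". Primary outcome (clinical) says that "The pre-enrollment score will serve as a covariate in a secondary analysis of the primary outcome"; the article also reserves that score for subanalyses.

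**The concern.** Because the clock starts at treatment, the outcome is remaining illness. Two children with the same total illness can differ by up to 72 hours in this outcome only because one came to the emergency department sooner. With a total of 120 h (an illustrative figure), entry at onset leaves 120 h and entry just short of 72 h leaves about 48 h. That spread is knowable at baseline, but neither randomization nor the named test uses it.

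At stake is power for two of the three secondary outcomes that are given a specific named test. Duration is one of the listed study questions under Clinical efficacy, and the article sets no sample size for it, so efficiency of the analysis is the main lever left.

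**Working it through.** **The plan's own figures.** The article gives no SD, effect size or power for the durations; its sample size concerns the primary outcome only. For 25% against 15%, two-sided alpha 0.05 and power 0.90, the pooled two-proportion formula gives 335 per arm, or 670, as stated. One reading of the inflation, 670 / 0.90 / (1 − 0.05 − 0.025)² × 1.02, gives 887.5, close to the stated 886. Neither figure depends on this point.

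**Inputs for the check.** Evaluable children: 886 × 0.90 / 2, about 398 per arm. The correlation ρ between elapsed time and remaining duration is not in the documents, so it is varied.

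**Analytic range.** Linear adjustment for a baseline variable removes a share ρ² of the outcome variance. The equivalent sample size is 1 / (1 − ρ²). If unadjusted power is 80% at alpha 0.05, adjusted power is Φ(2.802 / √(1 − ρ²) − 1.960).

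| absolute ρ | variance removed | equivalent sample size | power, from 80% |
|---|---|---|---|
| 0 | 0% | 1.00 | 80.0% |
| 0.1 | 1% | 1.01 | 80.4% |
| 0.2 | 4% | 1.04 | 81.6% |
| 0.3 | 9% | 1.10 | 83.6% |
| 0.4 | 16% | 1.19 | 86.4% |
| 0.5 | 25% | 1.33 | 89.9% |

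**Simulation, gamma illness length.** All settings are assumed: 797 children, five centers, entry uniform over 0–72 h, mean total illness 100 h before selection, and 3,000 trials per row (1,500 under the null). The effect shortens remaining duration by 18%, 17%, 13% and 11% from top to bottom, so comparisons are within rows. Bands are 0–24, 24–48 and 48–72 h.

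| rank correlation | Van Elteren by center | rank ANCOVA within center | Van Elteren by center × band |
|---|---|---|---|
| 0 | 66% | 66% | 65% |
| −0.14 | 78% | 79% | 77% |
| −0.30 | 71% | 75% | 74% |
| −0.48 | 73% | 83% | 82% |

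Type I error lay between 4.4% and 5.7% for all three methods, with a Monte Carlo standard error of √(0.05 × 0.95 / 1500) = 0.6 points.

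**Simulation, lognormal illness length.** Mean 120 h, 399 per arm, entry uniform over 0–72 h, 1,000 trials per setting, center × three time bands against center alone. The efficiency ratio was 1.23 at SD 40 h (correlation −0.44), 1.09–1.10 at SD 60 h (−0.28) and 1.01–1.03 at SD 90 h (−0.12). With exponential illness length (correlation 0) it was 0.97–0.99, which is the 1–3% downside of banding. The two illness models agree.

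**Holm.** The figures above use alpha 0.05. If Holm covers the three secondary tests named, its first step is 0.05 / 3. A test with 80% power at 0.05 then has Φ(2.802 − 2.394) = 66%. Efficiency ratios of 1.10 and 1.19 raise this to Φ(2.802 × √1.10 − 2.394) = 71% and Φ(2.802 × √1.19 − 2.394) = 75%.

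**Why the pre-enrollment score does not fill the gap.** Its stated covariate use is for the primary outcome. For diarrhea it could not help in any case: Table 1 gives one point for anything from 1 to 96 hours, so children with 5 and with 70 hours of diarrhea score alike. Only the vomiting item has bands that resemble elapsed time.

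**The case against.** The strongest reply is that nothing here is wrong. Stratifying the test by the randomization stratum is standard, the test holds its level, and prognostic covariates for secondary outcomes are often left to an analysis plan that is not shown. Validity is fully granted. But the article does name the test and its only stratum, so the point concerns a stated choice and not an omission.

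A second reply is that the closing regression models already adjust for baseline characteristics. The mention of linear models makes it plausible that the durations are covered, although the wording may refer only to the dichotomous outcomes listed just before. Either way they are additional, name no covariate and do not decide the outcome.

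Third, the gain rests on assumptions, and uniform entry over 0–72 h favors it. With remaining duration as total minus elapsed time, and the two independent, the variance explained is SD(entry)² / (SD(entry)² + SD(total)²). For total SDs of 40, 60 and 90 h it is 21%, 11% and 5% with entry over 0–72 h (SD 20.8 h). With entry over 24–72 h (SD 13.9 h) it is 11%, 5% and 2%. That roughly halves the benefit, and it stands as a reason to quote a range.

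Fourth, eligibility needs only a yes or no on the 72-hour limit, so hours for each symptom may not be on the form. This also stands; collection is an inference from Inclusion criteria, Implementation and the pre-enrollment score.

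Fifth, vomiting was not simulated. Its subset is smaller, and children who never vomit again could tie at zero. No figure above should be read as applying to it.

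**Conclusion.** The point holds as one of precision. For diarrhea duration, adjusting for elapsed time would add between nothing and about 10 power points for absolute correlations from 0 to 0.5, and about 2 to 4 points at 0.2 to 0.3, on assumed illness lengths and entry times. For vomiting the direction of the argument is the same but the size is unknown.

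A reader might infer that the duration comparisons are biased, or that chance imbalance in time since onset is a separate harm. The documents do not support either. Randomization makes such imbalance part of the sampling variation that the test already allows for; it is the same loss of precision seen from another side. Nor do they support any single figure for the gain, or the statement that hours since onset are known to be recorded. The primary analysis and the sample size of 886 are not touched. The change is worth making because it is cheap and its downside is small.

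**What to change.** In Statistical analysis, Clinical, state before unblinding that each duration is tested by a rank ANCOVA stratified by center, with pre-enrollment hours of that same symptom as the covariate. This needs no small strata and no merging rule. The alternative is a Van Elteren test stratified by center and elapsed-time band (under 24, 24 to under 48, 48 hours or more), with a minimum stratum size and a merging order fixed in advance. Leave Holm's adjustment unchanged.

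Confirm first that hours since onset of diarrhea and of vomiting are on the baseline form. If they are, the cost is wording only; if not, two items must be added, and children already enrolled would lack them (152 at the date given under Trial status). The statistical cost, if elapsed time proves not to be prognostic, is about 1–3% efficiency for the banded version; in the simulation at zero correlation, rank ANCOVA lost nothing visible.
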